## Abstract

**Background:**

Unilateral peripheral vestibular loss results in gait and balance impairment, dizziness and oscillopsia. Vestibular rehabilitation benefits patients but optimal treatment remains unkown. Virtual reality is an emerging tool in rehabilitation and provides opportunities to improve both outcomes and patient satisfaction with treatment. The Nintendo Wii Fit Plus^® ^(NWFP) is a low cost virtual reality system that challenges balance and provides visual and auditory feedback. It may augment the motor learning that is required to improve balance and gait, but no trials to date have investigated efficacy.

**Methods/Design:**

In a single (assessor) blind, two centre randomised controlled superiority trial, 80 patients with unilateral peripheral vestibular loss will be randomised to either conventional or virtual reality based (NWFP) vestibular rehabilitation for 6 weeks. The primary outcome measure is gait speed (measured with three dimensional gait analysis). Secondary outcomes include computerised posturography, dynamic visual acuity, and validated questionnaires on dizziness, confidence and anxiety/depression. Outcome will be assessed post treatment (8 weeks) and at 6 months.

**Discussion:**

Advances in the gaming industry have allowed mass production of highly sophisticated low cost virtual reality systems that incorporate technology previously not accessible to most therapists and patients. Importantly, they are not confined to rehabilitation departments, can be used at home and provide an accurate record of adherence to exercise. The benefits of providing augmented feedback, increasing intensity of exercise and accurately measuring adherence may improve conventional vestibular rehabilitation but efficacy must first be demonstrated.

**Trial registration:**

Clinical trials.gov identifier: NCT01442623

## Background

Unilateral peripheral vestibular loss (UVL) results in disabling problems including vertigo, dizziness, oscillopsia, and impaired balance and gait [1,2]. In the acute phase most patients are managed at primary care level and recover through a process known as vestibular compensation [3]. Pharmacological treatments are recommended only in the acute phase [4] and the mainstay for treatment thereafter in those who do not recover, is specialised rehabilitation known as vestibular rehabilitation. Vestibular rehabilitation is a safe, effective and non-invasive treatment for the sequelae of UVL [5,6]. Subjectively, balance impairment is rated as more problematic than dizziness or vertigo [7] and while meta-analysis has demonstrated a clear benefit for the reduction in dizziness and vertigo symptoms, a less convincing effect has been shown for reducing balance and gait impairment [5,8]. Most studies have measured the outcome of vestibular rehabilitation on subjective symptoms, static balance, and visual acuity during head movement and but have not measured in any detail its effect on gait impairment. Galvanic vestibular stimulation studies have shown that the vestibular system plays a phase dependent role in gait and is active at critical points in the gait cycle, particularly during double support, changing direction, and step termination [9]. Bent et al [9] concluded that "rehabilitation strategies should focus on compensating for deficient vestibular inputs during the gait cylce".

Rehabilitation of gait and balance during a vestibular rehabilitation program requires motor learning and thus practice and feedback. In conventional rehabilitation it is difficult for patients to gain feedback when performing balance exercises which can be repetitive and boring. Force plate technology has been used in the clinical setting to provide visual and auditory feedback during balance re-education and has shown some promising results [10,11]. Virtual reality, defined as a high-end-computer interface that involves real time simulation and interactions through multiple sensorial channels' [12] is also being investigated in laboratory settings [13]. Virtual reality provides feedback and also allows a more stimulating and enriching environment than usual rehabilitation. It can measure and track exercise, and allows virtual experience of activities the patient might otherwise not attempt [14].

There is some support for the use of virtual reality in vestibular rehabilitation [15] but most technologies are presently prohibitively expensive, considered to be for research use, and are not universally available. They require considerable therapist time and are unlikely to be used with the frequency that is required for motor learning, particularly in vestibular rehabilitation where most programs entail daily exercise. Recent developments in the gaming industry have resulted in the Nintendo Wii^® ^Fit Plus (NWFP, Figure 1). The NWFP combines an accelerometer and a forceplate to provide visual and auditory feedback of subjects' centre of pressure during virtual reality exercises and games. It stimulates movement and perturbs balance in order to retrain it. Use of this low cost gaming system could easily be adapted to meet the requirements of a vestibular rehabilitation program. The system allows for accurate monitoring of use (intensity, type and frequency) which is an important area that has proven difficult to monitor in research and clinical settings due to inaccurate patient recall or records. It is also fun to use and therefore motivating for the patient.

**Figure 1 F1:**
[figure not shown]
**The Nintendo Wii Fit Plus^®^**.

**The Nintendo Wii Fit Plus^®^**. The participant stands on the Wii balance board which monitors centre of pressure and reconstructs it visually on the television monitor as a red dot within a yellow area. A variety of exercises and games are available to retrain balance and encourage head movement. Stepping exercises can also be performed encouraging stopping and changing direction, in which the vestibular system has a role. Written consent to reproduce the image was provided by the subject in the photo.

The rehabilitation community is beginning to investigate the NWFP in the area of balance retraining [16,17]. Anecdotal reports indicate the NWFP is being used in vestibular rehabilitation [18] but as yet no randomised controlled trials exist. Importantly, Clark et al [19] recently showed that the NWFP force plate (Wii Board) tracks the centre of pressure with a similar accuracy to a gold standard forceplate. This provided initial support for the use of the NWFP in rehabilitation. Additionally we have shown that patients with vestibular problems found the NWFP highly usable, enjoyable and the majority of them preferred it to conventional balance re-education [20]. As yet no study has investigated the efficacy of the NWFP in vestibular rehabilitation. The aim of this study is to compare the outcome from conventional vestibular rehabilitation to virtual reality based vestibular rehabilitation using the Nintendo Wii Fit Plus^®^.

### Pilot study

As there are no reports of Nintendo Wii^® ^use in vestibular rehabilitation, a pilot study was carried out to investigate patient experiences with the NWFP^® ^[20]. The study found high levels of usability, acceptance and enjoyment of the NWFP^® ^as a therapy. The study assessed 26 participants with balance impairment (14 of whom had vestibular disease) performing NWFP^® ^exercises and games that will be incorporated as part of the proposed study and evaluated safety andsymptoms provoked. The average verbal rating scale for enjoyment (with higher scores indicating more enjoyment) was 8/10. The average System Usability Score [21] was 82% indicating high usability (defined as the learnability, ease of use and memorability of a system). Most (88%) participants reported they would like to use it in future treatment; 67% reported more enjoyment and motivation than conventional therapy. There were no significant adverse effects but for safety purposes patients required additional haptic support during exercise (in the form of a chair) [20].

## Methods/Design

The study protocol has been designed with reference to the CONSORT statement in order to ensure methodological validity [22]. It is not possible to blind treating therapists nor patients to the treatment intervention so a single (assessor) blind, randomised controlled trial design will be used. It is also considered unethical to have a "no treatment" or a placebo control group as treatment for peripheral vestibular dysfunction has a robust evidence base [5]. The aim of this study is to compare the outcome from conventional vestibular rehabilitation to virtual reality based vestibular rehabilitation in the treatment of peripheral vestibular impairment. A parallel design will be used. Figure 2 shows the flow of diagram of the trial.

**Figure 2 F2:**
[figure not shown]
**CONSORT (2010) flow diagram of the trial**.

Study objectives

1. To compare the effect of conventional vestibular rehabilitation and virtual reality based rehabilitation on gait impairment.

2. To compare the effect of conventional vestibular rehabilitation and virtual reality based rehabilitation on balance.

3. To compare the effect of conventional vestibular rehabilitation and virtual reality based rehabilitation on dizziness and vertigo.

4. To compare the effect of conventional vestibular rehabilitation and virtual reality based vestibular rehabilitation on dynamic visual acuity.

5. To quantify and compare patient satisfaction and adherence with conventional and virtual reality based vestibular rehabilitation.

### Participants and setting

Patients attending the otolaryngology and neurology outpatient clinics in two Dublin university teaching hospitals (Beaumont Hospital, Dublin and the Royal Victoria Eye and Ear Hospital, Dublin) for diagnosis and treatment of unilateral vestibular loss will be invited to participate in the trial. Participants will be provided with information leaflets and given a cooling off period to consider their involvement in the trial. Written informed consent will be obtained and patients will be free to withdraw from the study at any time. Non-consenting participants will be treated with usual care.

### Inclusion criteria

Participants will be included if they have a clinical diagnosis of peripheral vestibular dysfunction (confirmed where possible with vestibular function testing; canal paresis > 20%), and no other neurological deficit. Caloric testing is not available to all patients in the sites; where it is not available presence of a positive head thrust test, head shaking after nystagmus or spontaneous nystagmus (assessed with infrared oculomotor recording system) will be used to support the clinical diagnosis. Participants will also have one of the following subjective complaints indicating a failure of vestibular compensation; dysequilibrium, gait instability, vertigo/dizziness, or motion sensitivity.

### Exclusion criteria

Participants will be excluded if they have had previous vestibular rehabilitation or have bilateral peripheral vestibular pathology, CNS involvement, fluctuating symptoms Meniere's disease, migrainous vertigo), active benign paroxysmal positional vertigo, or other medical conditions in the acute phase (orthopaedic injury). As per Nintendo Wii^® ^guidelines, participants will also be excluded if they have a pacemaker or epilepsy, or are unwilling or unable to use a NWFP. Pregnant patients will also be excluded.

### Outcome measures

Consenting participants will complete baseline assessments prior to randomisation. They will be retested post treatment (at 8 weeks). The primary endpoint is gait velocity (m/sec) at 8 weeks post baseline.

Gait velocity will be assessed using three dimensional gait analysis (3DGA) in the Royal College of Surgeons in Ireland, School of Physiotherapy's Movement Laboratory. The laboratory has a Vicon 250 motion analysis system (Vicon Motion Systems Ltd., Oxford, UK) and a Kistler force plate (Kistler Instruments Ltd., Winterthur, Switzerland). Vicon consists of five infra red cameras that are able to localize reflective markers (placed on the participant) in a three-dimensional coordinate system within 1.5 mm error. Because of its high level of accuracy and reliability, it is considered a "gold standard" for motion analysis. The Kistler force plate, in synchronicity with the Vicon is able to compute kinetic forces during gait as well as centre of mass and centre of pressure. Gait velocity will be recorded during four conditions; self selected speed eyes open, self selected speed eyes closed (towards a target), cadence of 120 steps per minute eyes open (paced with a metronome), and walking with head turns.

Secondary gait variables will also be investigated; percentage of a gait cycle spent in double support, base of support width (cm), centre of mass/centre of pressure moment arm (mediolateral) and centre of mass velocity and displacement. These variables have been identified by Krebs et al (2003) [8] as the most significant discriminators of success following vestibular rehabilitation The Dynamic Gait Index (DGI)[23] will also be assessed.

Other secondary outcomes will be;

1. Computerised dynamic posturography (Equitest-NeuroCom) [24]. This measures postural sway during six sensory conditions and returns sensory ratios that can be compared to normative data. The sensory organisation test (SOT) will be performed according to the protocol published by Equitest (Neurocom).

2. The Vestibular Rehabilitation Benefits Questionnaire (VRBQ) [25,26] and the Activities Specific Balance Confidence Scale (ABC) [27]. These are validated and reliable questionnaires for assessment of the effects of dizziness. Scores range from 0-100.

3. Dynamic Visual Acuity (DVA) [28]. This will be measured using a computerised DVA test (Micromedical Technologies, Chatham, Illinois). The difference between static and dynamic visual acuity (at three head speeds) in LogMAR units will be measured using the protocol published by Micromedical Technologies.

4. The Hospital Anxiety and Depression Scale (HAD) [29]. This validated scale has been used previously in studies in vestibular rehabilitation and assesses non-somatic symptoms of anxiety and depression. Scores range between 0 and 21, scores between 8 and 10 are considered borderline and those above ten indicate clinical depression or anxiety.

5. Usability of virtual reality technology will be measured by the System Usability Questionnaire [21]. This is a 10 item questionnaire using Likert scales. Adherence will be recorded in the exercise booklets (and where allocated, on the NWFP) and satisfaction with treatment will be measured with a questionnaire developed by the researchers.

A six month follow up will be carried out. This will be confined to the primary outcome measure of gait velocity (m/sec), and secondary outcomes of computerised posturography, the VRBQ, ABC and DGI. Outcome measurement at each time point is shown in Table 1.

**Table 1 T1:** Time frame and outcome measures in the study

Outcome Measure	Baseline Assessment	Post treatment (8 weeks)	Post Treatment (6 months)
Gait Speed	**✓**	**✓**	**✓**
Dynamic Gait Index	**✓**	**✓**	**✓**
Dynamic Posturography	**✓**	**✓**	**✓**
Activities Balance Confidence Questionnaire	**✓**	**✓**	**✓**
Vestibular Rehabilitation Benefits Questionnaire	**✓**	**✓**	**✓**
Dynamic Visual Acuity	**✓**	**✓**	
Hospital Anxiety and Depression Scale	**✓**	**✓**	
Adherence/Satisfaction with treatment			
*Three Dimensional Gait Analysis*			
Centre of mass velocity and excursion	**✓**	**✓**	
Centre of mass/centre of pressure moment arm	**✓**	**✓**	
% gait cycle in double support	**✓**	**✓**	
step width (cm)	**✓**	**✓**	

### Sample size and power calculation

Based on previously published work the estimated sample sizes for each outcome variable have been calculated (Table 2). The calculations were performed to detect what would be a clinically important difference between the means, with a significance level of 0.05 using the power calculation by Pocock [30] given as;

**Table 2 T2:** Sample size and power calculations for the trial

Outcome Measure	Mean Change Expected	SD	Sample Size Required (per group)
Gait Velocity (m/sec)	0.1	0.15	36
Vestibular Rehabilitation Benefit	-7	10.1	33
Questionnaire (%) [25]			
Static Posturography (% composite score)[31]	10	15	36
Dynamic Visual Acuity (LogMAR) [32]	0.1	.136	30

$$\text{n}=\frac{2\sigma^{2}}{{\left(\mu_{2}-\mu_{1}\right)}^{2}}\times \text{f}(\alpha ,\beta )$$

Where σ is the standard deviation, μ is the mean difference expected between the two groups using a two sample t-test, α is the significance level (P < 0.05) and β is the lower (0.80) and f (α,β) is 7.9. Allowing for a 5% drop-out rate a minimum of 37 patients will be required pergroup. Current referral rates of patients with unilateral vestibular loss to physiotherapy approximate 40-50 participants per year over the two sites, thus a two year recruitment period is required.

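### On the plan's own inputs the minimum is 38 per group, not 37 (harmless if 80 are randomised); β is misprinted, and 80 patients in two years needs 80–100% of referrals

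*Protocol article*

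**What the plan says.** Under Sample size and power calculation, Table 2 gives 36 per group for gait velocity, from a difference of 0.1 m/sec and an SD of 0.15. The power terms are described as "β is the lower (0.80) and f (α,β) is 7.9", and the calculation is for a two-sample t-test at a significance level of 0.05. The drop-out allowance follows: "Allowing for a 5% drop-out rate a minimum of 37 patients will be required pergroup".

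The section closes with recruitment. Physiotherapy referrals with unilateral vestibular loss "approximate 40-50 participants per year over the two sites, thus a two year recruitment period is required".

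The abstract (Methods/Design) gives the planned size: "80 patients with unilateral peripheral vestibular loss will be randomised". The sample size section does not mention 80. Under Participants and setting, consent is voluntary and those who decline receive usual care. Exclusion criteria lists several grounds for exclusion, including earlier vestibular rehabilitation, a pacemaker, epilepsy, pregnancy, and being unwilling or unable to use the device. No eligibility or consent rate is given.

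**The concern.** A stated minimum is the number a trial team can point to when deciding whether recruitment is complete. If it is lower than the plan's own inputs require, a trial that stops there falls below its own evaluable target. Printing β as 0.80 makes the power statement wrong as written, and a reader who tries to reproduce it literally will fail.

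The recruitment sentence moves directly from a count of referrals to a recruitment period. Referrals are not enrolments, and the protocol itself provides for patients who are excluded or who refuse. What is at stake is mainly the timetable. Power is affected only if recruitment were to stop short of the planned 80.

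**Working it through.** **Inputs.** From the sample size section and Table 2: difference 0.1 m/sec, SD 0.15, α = 0.05, f = 7.9, drop-out 5%, 40–50 referrals per year. From the abstract: 80 randomised. Two things are assumed because they are not stated: a two-sided test (supported by f, since (1.960 + 0.842)² = 7.85, whereas a one-sided test would give about 6.18) and 1:1 allocation.

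**1. Reproducing Table 2.** n = 2 × 0.15² / 0.1² × 7.9 = 35.55, rounded up to 36. The other three rows also reproduce (33, 36 and 30).

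**2. Drop-out allowance.**
- 36 / 0.95 = 37.89, so 38.
- 36 × 1.05 = 37.8, so 38.
- Unrounded: 35.55 / 0.95 = 37.42 and 35.55 × 1.05 = 37.33. These give 37 only if rounded to the nearest whole number. A minimum is rounded up, which again gives 38.

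**3. Effect of one patient fewer per group.** Expected evaluable per group at 5% loss, with power by the plan's normal approximation:

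| Randomised per group | Evaluable at 5% loss | Power |
|---|---|---|
| 37 | 35.15 | 79.8% |
| 38 | 36.1 | 80.9% |
| 40 | 38.0 | 82.8% |

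With 40 per group, 36 remain evaluable at a loss of up to 1 − 36/40 = 10%.

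**4. β.** With β = 0.20, f = (1.96 + 0.84)² ≈ 7.85, which the plan gives as 7.9. Read literally, β = 0.80 gives f ≈ (1.96 − 0.84)² = 1.25 and n = 2 × 0.15² / 0.1² × 1.25 = 5.6, or 6 per group. Table 2 was therefore computed for 80% power, and only the printed β is wrong.

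**5. Recruitment.** Two years give 2 × 40 = 80 to 2 × 50 = 100 referrals. Share of referrals that must enrol:

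| Target | At 50 per year | At 40 per year |
|---|---|---|
| 80 (abstract) | 80/100 = 80% | 80/80 = 100% |
| 76 (38 per group) | 76/100 = 76% | 76/80 = 95% |
| 74 (37 per group) | 74/100 = 74% | 74/80 = 92.5% |

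At 40 referrals per year, a single exclusion or refusal puts 80 out of reach within two years.

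**6. Illustration only.** The document gives no uptake fraction, so the fractions here are assumptions. Time to 80 is 80 / (referrals per year × fraction):
- 90%: 80/45 = 1.8 to 80/36 = 2.2 years
- 80%: 80/40 = 2.0 to 80/32 = 2.5 years
- 70%: 80/35 = 2.3 to 80/28 = 2.9 years
- 60%: 80/30 = 2.7 to 80/24 = 3.3 years

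**The case against.** The best reply is that nothing here harms the trial as planned. The figure of 37 is called a minimum, and 40 per group exceeds both 37 and 38. On the plan's own method the gap is about 0.2 points below 80%. The β entry is garbled wording that affects no number. All of this stands, and it is why the point is minor.

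A reader might infer that the document carries two conflicting targets, 74 and 80. It does not: a planned size above a stated minimum is consistent with it. What remains is that the section does not link the two, and a condensed article may leave that out.

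A reader might also quote a larger power loss from an exact t calculation, which gives 78.7% at 35.15 evaluable. That sets one method against a target derived by another. By exact t the plan's own 36 also falls short (79.7%); 37 evaluable would be needed, or 39 after 5% loss (37/0.95 = 38.9), and 40 per group still covers that.

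It can further be said that the intention-to-treat analysis carries the last observation forward, so drop-outs stay in it. That is true, but the sample size section makes an allowance for drop-out, and that allowance should be computed correctly.

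On recruitment, the referral count is already limited to unilateral vestibular loss, so some exclusions may be partly applied. Patients are invited from otolaryngology and neurology clinics, and the document does not say that physiotherapy referrals cap that pool. Both observations soften the point. They do not remove it, because the plan itself bases the two years on that count and states no uptake fraction.

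**Conclusion.** The point holds as a minor one, in three parts.

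- **Minimum:** 37 should be 38. The error is one patient per group and has no power consequence if 80 are randomised.
- **β:** the printed 0.80 should be 0.20 (power 0.80). No result changes.
- **Recruitment:** the two-year period needs 80–100% of referrals to enrol for 80 patients, or 74–92.5% for 74. This is the part with practical weight, because the margin for exclusions and refusals is small, and nil at 40 referrals per year.

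It is tempting to conclude that the trial will be underpowered, for example that 70% uptake would yield 56–70 patients and 69–79% power (exact t, before drop-out). The document does not support this. The 70% is an assumption, and the loss also needs recruitment to close at two years whatever the numbers, a rule the protocol does not state. Slow accrual could equally mean a longer trial.

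The figures assume a two-sided test, 1:1 allocation, and that the quoted referrals are the pool from which patients are enrolled.

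**What to change.** Replace the drop-out sentence and the β entry with wording such as: *36 evaluable per group (α = 0.05, β = 0.20, power 0.80); at least 38 per group at 5% drop-out; 80 patients (40 per group) will be randomised, which keeps 36 per group at up to 10% loss.*

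Restate the recruitment period as 80 / (40–50 referrals per year × the expected eligible-and-consenting fraction). Write that fraction down with its basis, and say that recruitment continues until 80 are randomised. Label any durations or power figures at assumed uptake rates as illustrative.

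The cost is a text correction with no patients beyond the 80 already planned. The downside is a longer stated recruitment period wherever the fraction falls below the 80–100% that two years requires.
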